### Study design

Our study will employ a quantitative case-control study approach [27]. Adoption and sustained use of technology (such as LPG) by poor communities has a long latency period, and is impacted by multiple parameters from social, economic, and technological domains [28]. Case-control studies are suited for such phenomena, which have a long latency period [27]. These studies are relatively inexpensive to implement, and allow for concurrent analysis of multiple determinants [27]. Our study will test the conceptual model shown in Fig. 1.

**Fig. 1 Fig1:**
[figure not shown]
Impact of 3As on adoption and sustained use of LPG. This figure is a visual representation of the conceptual model arguing the concurrent role of affordability, accessibility, and awareness in fostering adoption and sustained use of LPG in poor communities. This study will test the validity of this model

Different stove adoption related studies have defined adoption and use in ways specific to their studies. It is imperative to define the five concepts illustrated in Fig. 1. Definitions of these concepts as they pertain to this study are:
*Awareness* refers to the degree of knowledge and perception about LPG adoption and use [19]. Several studies recognize the significance of awareness in motivating households for a fuel switch [19, 22]. Scattered evidence suggests that low information and scattered rumors on LPG safety issues may act as a deterrent to uptake and use of LPG by these rural households [23]. Measures of affordability, accessibility, and awareness are predictors of outcome variables of adoption (aim 1) and sustained use (aim 2) in this study. To further explore impact of awareness, we will also conduct social network analysis (aim 3) to assess how knowledge and awareness flows through social networks and consequently impacts the decision to adopt LPG among households.
*Accessibility* of LPG indicates factors impacting a household’s ability to procure LPG cylinders and stoves when needed. Factors affecting accessibility include (but are not limited to) distance to rural LPG distribution center, delivery mechanism of LPG cylinders, and road connectivity from villages to local distribution centers [23].
*Affordability* refers to the maximum possible capacity of households to pay for the minimum level of services [23]. Affordability is impacted by household factors such as income and LPG demand, and also by government policies on LPG subsidies [23].
*Adoption* refers to the initial uptake of LPG [29, 30]. Adoption of LPG is independent of the behavioral phenomena of sustained use of LPG or stacking LPG with traditional stoves. Adoption of LPG is a dichotomous outcome variable (LPG adopter households/LPG non adopter households) in this study (aim 1).
*Sustained use* shows the degree to which LPG is used and has been integrated in daily behavior of users [29, 30]. Sustained users who exclusively use LPG make a complete switch to LPG with no intention of reverting to traditional stoves or traditional fuels [29]. Stackers are those households who combine use of LPG with traditional stoves. We study the degree of use of each of these stoves for a select number of households (from group: LPG adopters) by using the Stove Use Monitor Systems (SUMS) technology. SUMS are based on commercially available temperature loggers, which record the variation in the stove temperature over a defined period of time to provide accurate insights into stove usage patterns, duration of use, and number of meals cooked. There are numerous models of SUMS available. For this study we are using iSUMS model DS 1922 L, which can record data for as long as 4–6 weeks post installation on the stoves [31]. Sustained use of LPG is a continuous outcome variable (aim 2). We measure this variable with the help of SUMS technologies, which will record the number of hours of use of LPG stoves and of traditional stoves. For analysis, we can also dichotomize sustained use into two categories: exclusive LPG users, and stackers. Households which use LPG at least 80% of the total cooking duration during our monitoring period (recorded with SUMS technology) will be characterized as exclusive LPG users. Such a metric will allow us to compare the results of this study with other LPG adoption studies now underway in different parts of the world [32];

### RE-AIM evaluation framework

RE-AIM is a systematic framework, which expands the assessment of a social or a public health intervention, evaluates its potential for translating research into practice and policy, and bridges the research-practice gap [33, 34]. The different aims of our study find a larger meaning and value when framed within the RE-AIM framework. RE-AIM stands for **R**each, **E**ffectiveness, **A**doption, **I**mplementation, and **M**aintenance. The five dimensions of the RE-AIM framework provide a way to synthesize the findings from across our three aims of the study: 1) **R**each is a measure of participation [34]. It refers to the proportion of the target population that has participated in the intervention [34]. Reach is concerned with the characteristics of the participants and whether they truly represent the target population [33, 34]. In understanding the rural poor LPG users now being reached, we stand to gain insights on how the program may improve its reach to larger proportion of rural poor households. We collect these demographic characteristics in aim 1 of the study; 2) **E**ffectiveness refers to the success rate of the health intervention, if implemented [33, 34]. The evidence based technology in our study is LPG. The effectiveness of LPG has been established by the WHO. LPG meets all the required IAQG [8]; 3) **A**doption refers to the absolute number or proportion of the target population who take up an evidence based health intervention [34]. Adoption is usually assessed by direct observation or structured interviews [34]. We examine adoption of LPG in aim 1 of the study. We examine affordability, accessibility, and awareness (3As) in aim 1 and relative influence of gender networks on LPG adoption in aim 3, to examine the predictors impacting adoption of LPG [9, 23, 35]; 4) **I**mplementation refers to fidelity in LPG use, and adherence of distribution programs in LPG delivery as intended [33, 34, 36]. Through structured interviews, we examine the 3As in aim 1 to assess if the LPG distributors reliably provide LPG permits and cooking fuel to meet the needs of the participants, as per demand and within policy and program guidelines; 5) **M**aintenance measures the extent to which the intervention has been integrated into the routine practices of the participants [34]. It is accompanied by a change in the practice patterns of the participants to sustainably integrate the health intervention in their routine practices without any intention of abandonment [34]. In this study, we assess maintenance in aim 2 by deploying SUMS technologies over 12 months to examine the extent of sustained use of LPG.

The RE-AIM framework emphasizes multilevel and concurrent examination of household and organizational level factors driving adoption, implementation, and maintenance of health interventions, instead of an isolated examination of such levels [33, 34, 36]. It seeks to address the ‘voltage drop’ as interventions move from efficacy testing to real world sustainment [37]. The barriers and enablers of adoption and use occur at individual and possibly at organizational levels. The study protocol allows us to examine both these levels [34]. Similarly, individual and organizational level factors may influence effectiveness of an intervention [34, 36]. While affordability is a household level factor, accessibility and awareness of LPG cut across household and organizational level factors. RE-AIM framework allows us to examine how affordability, accessibility, and awareness at multiple levels influence adoption and sustained use of LPG [33, 34, 36] in study aim 1 and study aim 2. In addition, gender networks in communities also influence uptake and use of health interventions [38]. Aim 3 explores the relative influence of personal gender networks of males and females in selected households and their impact on LPG adoption. Figure 2 synthesizes the placement of the three aims and analyses of our study within the RE-AIM framework.

**Fig. 2 Fig2:**
[figure not shown]
RE-AIM framework to analyze determinants of adoption and sustained use of LPG. This study is guided by the RE-AIM (Reach, Effectiveness, Adoption, Implementation, and Maintenance) implementation science framework. This protocol paper highlights the application of the RE-AIM framework in our study of LPG adoption and sustained use in poor households. This figure synthesizes the placement of the three aims and corresponding analyses of the study within the RE-AIM framework

The dissemination of LPG cooking systems in these energy poor communities are undertaken as part of pro-poor projects by the state government and national government in India to reduce HAP. Evaluation of these government projects is crucial as the Government of India has plans to scale up and adopt strategies to push LPG to the rural interiors of the country. A successful scale up requires a nuanced understanding of multiple factors impacting the intervention. This study is situated within the domain of implementation science, and will employ the RE-AIM evaluation framework to systematically explore the factors impacting adoption of LPG. The study will examine multiple household, organizations, and network related drivers that could enable LPG adoption. These factors could be tested in multiple geographies to strengthen the evidence base for scaling up LPG dissemination. It is expected that the study will provide evidence that there are multiple and concurrent determinants of LPG adoption. Understanding and addressing these determinants is crucial for fostering adoption of cleaner cooking systems such as LPG in energy poor communities. Using the RE-AIM framework to undertake this study serves two purposes: 1) factors analyzed against each of the RE-AIM dimensions will be available to frame and study adoption and sustained use of cleaner cooking systems in other geographies and contexts; and 2) factors examined in this study could then be tailored and tested in the adoption of other evidence-based interventions to improve the health and wellbeing of poor communities. For instance: sustained use of contraceptives in Uganda, toilets in Bangladesh, mosquito nets in parts of Africa, and mobile technologies in rural India.

### Sampling and recruitment

We will undertake a case control study in the rural habitations of Thambalpalle and Peddamandyam mandals (block) in Chittoor district of Andhra Pradesh state in India [27]. Our implementing partner, Foundation for Ecological Security (FES) has extensive field experience working in this region and we will leverage their expertise and understanding of social, economic, and demographic characteristics of the households in these habitations.

We will select an equal number of case and control households for this proposed study (control to case ratio will be 1:1). We will select a sample size of 255 households each for case (LPG adopter households) and control (LPG non-adopter households). A total sample size of 510 households at a 95% confidence level (alpha = .05) will provide a power of 80% to this study at a control to case ratio of 1. This computation assumed that the populations mean difference in monthly income was 545.35 India National Rupee (INR), and the common within-group standard deviation was 2199.26 INR per month. In the absence of previously published studies on rural income in this region, where the study is to be undertaken, the power computation was conducted using a baseline income data from another recently concluded NIH funded R21 (WUSTL IRB ID# 201207016) randomized controlled trial (RCT) on cookstoves. This study will be conducted in the same region where the RCT was undertaken. To calculate the sample size, we used the Power and Precision 4 software. The criterion for significance (alpha) was set at 0.05. The test was 2-tailed, and so an effect in either direction will be interpreted. With the proposed sample size of 255 each for case and control group, the study will have power of 80% to yield a statistically significant result. It is also assumed that this effect size is reasonable; an effect of this magnitude could be anticipated in this field of research. On average, a study of this design would enable us to report the mean income difference with a precision of 95% confidence level.

We use a multistage random sampling to select households in these rural habitations. To facilitate sample selection, we develop an exhaustive list of habitations (and households in these habitations) with four key variables: 1) distance to nearest LPG distribution center; 2) dominant caste of the habitation; 3) number of households in each habitation; 4) presence of LPG adopters in these habitations. A multistage sample selection process will be conducted using the following steps in their respective order:
**Sample of habitations:** We will use stratified random sampling to select the list of villages for the study. The selection criteria are:

*Proximity to the nearest LPG distribution center:* Based on the distance from the nearest LPG refilling and distribution center, we divide the exhaustive list of habitations (i.e. habitations population list) in two sub-groups: near to the center and far from the center, by taking a median split of the distance of the habitation from the LPG distribution center.
*Dominant caste of the habitation:* We divide the habitations population list into three sub-groups: General Caste, Other Backward Castes (OBC), and Scheduled Castes/Scheduled Tribes (SC/ST).

These two stratifying variables and their subgroups will lead to six distinct strata (2subgroups*3subgroups). We will divide the habitations population list across these six distinct strata. We will select a total sample of 35 habitations from these six distinct strata. Table 1 shows an indicative list of the six distinct strata that will be used to select the final 35 habitations.2.We have data on the number of LPG adopters and non-adopters from each of these selected habitations. We will use quota sampling to select households from each of these habitations. We will randomly select 255 LPG adopter households (case) from these 35 habitations. Subsequently, we will select as many non LPG adopter households (control) as we have LPG adopters (case) across each of the habitations. This will ensure a case control design in every habitation, with a control to case ratio as 1, and a total sample size of 510 households.

**Table 1 Tab1:** Exhibit list of stratified random sample of habitations

Strata	Proximity to LPG distribution centers	Dominant caste
1	Near	General
2	Near	OBC
3	Near	SC/ST
4	Far	General
5	Far	OBC
6	Far	SC/ST

In case we do not get the required sample size of 510 households in these 35 habitations, we will repeat steps 1 and 2 for selecting additional habitations to reach the required sample size.

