### Data analysis

#### Aim 1: To understand how rural LPG adopters vary from other rural households on factors of affordability, accessibility, and awareness of LPG

We will conduct preliminary univariate and bivariate data analyses. The categorical outcome variable for aim 1 (adoption of LPG: yes/no) will be regressed on the predictors (3As) recorded from the adoption questionnaire. We will have two levels of data from the household adoption questionnaire covering information on the 3As: level 1) household level characteristics such as income, women’s financial autonomy, household size, or caste; and level 2) community level characteristics such as LPG cylinders’ home delivery facility, presence of paved roads, government promotion campaigns, or distance of LPG distribution centers from the habitation. Depending on the values of intra class correlation (ICC) coefficient (if higher than the accepted norm of 5%), we will conduct additional analyses. We will use these two levels of data to conduct a multilevel regression modeling (using R version 3.0.3) with habitations as grouping variable, to predict these higher-level influences of 3As on adoption of LPG among rural households. We will also analyze the interaction effect of 3As on LPG adoption.

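### Matching controls to cases 1:1 within each habitation leaves the planned habitation-level effects on LPG adoption (aim 1) unidentified and makes the 5% ICC check uninformative

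*Protocol article*

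**What the plan says.** Three statements in the protocol article bear on this.

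- *Sampling and recruitment*, on controls: "Subsequently, we will select as many non LPG adopter households (control) as we have LPG adopters (case) across each of the habitations". The next sentence puts the ratio at the level of the single habitation, not only of the whole sample: "This will ensure a case control design in every habitation, with a control to case ratio as 1". The same section sets 255 cases and 255 controls, and says of the habitations: "We will select a total sample of 35 habitations from these six distinct strata".
- *Data analysis, Aim 1* regresses adoption (yes/no) on affordability, accessibility and awareness at two levels. Level 2 consists of "community level characteristics such as LPG cylinders’ home delivery facility, presence of paved roads, government promotion campaigns, or distance of LPG distribution centers", the last measured for the habitation. The multilevel model is to be fitted "with habitations as grouping variable, to predict these higher-level influences of 3As on adoption of LPG among rural households". Additional analyses depend on an intraclass correlation above 5%.
- *Sampling and recruitment*, on what is known beforehand: "We have data on the number of LPG adopters and non-adopters from each of these selected habitations".

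Neither the aim 1 analysis nor *Limitations* says that the quota matches on habitation, and neither describes a correction for the sampling fractions.

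**The concern.** The sampling rule and the analysis work against each other. The quota sets the share of adopters to one half in every habitation, near or far, with or without a paved road. The level 2 analysis then asks whether adoption differs between habitations according to those features. The sample no longer holds that information.

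Two wrong conclusions could follow. An ICC at or below zero could be read as showing that community context does not matter, when the sampling produced it. And a level 2 coefficient from an adjusted model could be reported as an accessibility effect when it reflects the quota and the covariates. *Limitations* says the findings will inform effect sizes for a larger study, and *Discussion* directs the lessons at national LPG policy, so such an error would be carried forward.

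**Working it through.** **The plan's own figure.** The sample size rests on monthly income (difference 545.35 INR, SD 2199.26 INR, two-sided alpha 0.05, power 80%). n per group = 2 × (1.960 + 0.842)² × (2199.26/545.35)² = 255.3, which rounds up to 256; power at 255 is 79.95%. The stated 255 reproduces within rounding. It concerns a household variable and is not in dispute.

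**Inputs from the article.** 255 cases, 255 controls, 35 habitations, controls equal to cases in each. On average 510/35 = 14.6 households per habitation, 7.3 of each kind.

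**Unadjusted odds ratio.** Let habitation h supply m_h cases and m_h controls, and let z_h be a binary variable constant within h. Cases with z = 1 number A = Σ m_h over habitations with z_h = 1, and so do controls. Cases with z = 0 number B = Σ m_h over the rest, and so do controls. OR = (A × B)/(B × A) = 1. A continuous z likewise has the same distribution in cases and controls, so its log odds ratio is 0. No assumption about the true effect enters.

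**ICC.** Every habitation has mean adoption 0.5, so the between-habitation mean square (MSB) is 0. ICC = (MSB − MSW)/(MSB + (n − 1) × MSW) = −1/(n − 1) = −1/13.6 = −0.07. A model that bounds the variance at zero returns 0. Neither can exceed 5%.

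**Adjusted coefficient.** With a household covariate x of log odds ratio β, the quota forces each habitation's intercept to the value that makes the average fitted probability one half, roughly −β × (mean of x in that habitation's sample). The coefficient of z then mainly reflects −β × (difference in mean x between z = 1 and z = 0), not the effect of z.

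**Simulation.** 400 replicates per scenario. Assumed inputs, not from the article: 150 households per habitation, intercept −1.2, habitation SD 0.5 on the logit scale, β = 0.8. The model is a single-level logistic regression on a far/near indicator. Entries are mean estimated log odds ratios.

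| Controls | Model | True 0 | True −0.69 | True −1.39 |
|---|---|---|---|---|
| 1:1 within habitation | far/near only | 0.00 | 0.00 | 0.00 |
| 1:1 within habitation | plus x, same mean near and far | 0.00 | −0.07 | −0.12 |
| 1:1 within habitation | plus x, mean 0.5 lower in far | +0.36 | +0.31 | not run |
| No within-habitation quota | far/near only | 0.01 | −0.60 | −1.25 |
| No within-habitation quota | plus x, mean 0.5 lower in far | −0.03 | −0.66 | not run |

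In the first row the estimate was zero in every replicate. The third row agrees with the approximation above: −0.8 × (−0.5) = +0.40. There, with a true effect of 0, the coefficient was significant in 33.5% of replicates. Under the quota the ICC averaged about −0.07, was never above −0.063, and exceeded 5% in no replicate. Without the quota, in the unadjusted runs, it exceeded 5% in 41% to 98% of replicates. Under the quota the household coefficient was still recovered (about 0.80 for a true 0.80).

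**The case against.** The strongest reply is that matching on area is a recognised case-control choice. It controls habitation-level confounding, it leaves household effects intact, and the study is sized on a household variable. All of that stands. The study is also described as exploratory, and corrections by sampling fraction are details that an article may leave to a fuller plan. That explains a missing formula. It does not reconcile two stated elements that conflict: the quota, and a level 2 analysis with an ICC trigger on the same sample.

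A reader might go further than the documents allow in four ways.

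- *That accessibility and awareness as a whole are lost.* They are not. *Study design* defines awareness through knowledge and perception, *RE-AIM evaluation framework* places both constructs across household and organizational levels, and *Data collection, Aim 1* lists the household's own distance, self-help group participation and household-reported supply problems. These can vary within a habitation. Only the part constant within a habitation is affected.
- *That the reported effect will be zero.* This is exact for the unadjusted association. After adjustment the effect is not identified, and its estimate can take either sign.
- *That the RE-AIM adoption proportion is fixed at 50%.* The article gives the general definition but, for this study, speaks of predictors of adoption. It nowhere plans to take a proportion from the 510 households.
- *That case-control differences in roads or delivery within one habitation must be reporting differences.* This is conjecture. Nothing in the article says that delivery or campaign exposure is uniform within a habitation.

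**Conclusion.** The point holds for predictors that are constant within a habitation, and for the 5% ICC check. As written, the matched sample cannot estimate the former, and the latter cannot be met whatever the true community influence. The unadjusted odds ratio of 1 and the ICC of about −0.07 are algebra and need only the stated 1:1 rule and the average habitation size. Refusals could disturb the exact balance but would not bring the true effect back. The adjusted figures (−0.12 to +0.36 for true values between −1.39 and 0) rest on the assumed inputs. They show that the coefficient is unreliable and can have the wrong sign, and do not forecast its size in this study. The simulation used a single-level model, so its rejection rates are not power figures.

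Household-level predictors such as income, women's financial autonomy, self-help group participation and the household's own distance remain estimable, as do interactions between household-level and habitation-level variables. The article does not make clear which additional analyses depend on the ICC. If the multilevel model itself does, the plan would skip it because of a sampling artefact.

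**What to change.** 1. State that controls are matched to cases on habitation. Limit the uncorrected matched analysis to predictors that vary within a habitation and to cross-level interactions.
2. Drop the 5% ICC trigger on the matched sample.
3. Estimate habitation-level effects for the selected habitations from the counts described in *Sampling and recruitment*, in one of these ways:
   - a per-habitation offset in the household model, log(case sampling fraction / control sampling fraction). With N1 eligible adopters, N0 eligible non-adopters and m of each sampled, this is log[(m/N1)/(m/N0)] = log(N0/N1);
   - inverse-sampling-probability weights in the household model;
   - an overdispersed or random-effect binomial model of adopters out of all households per habitation. This gives a marginal effect, not the household-adjusted one, and should be labelled so.

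The cost is analysis wording and one extra or modified model, with no additional households. There are four conditions. The counts must follow the rules in *Study participants*, in particular a first cylinder within the last 12 months for cases; the article does not say that they do. Road and delivery status must be recorded once per habitation. Precision is limited by about 35 habitations. Extension to all listed habitations, including any without adopters, is possible only if adopter counts exist for them: for the full list the article names only whether adopters are present.
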